## Abstract

**Background:**

The prevalence of type 2 diabetes has increased dramatically in the last decade, and is continuing to rise. It is a chronic condition, often related to obesity, diet and sedentary lifestyles, and can lead to significant health complications, disability and early death. Diabetes is commonly associated with depression, which can impact significantly on a person’s ability to manage their illness and, consequently, on disease outcomes. Disease self-management is fundamental in diabetes and requires support from multiple health professionals and the active participation of the person, including in maintaining a healthy lifestyle. The Whole Person Model was developed in order to integrate emotional and behavioural aspects into a self-management program for people with type 2 diabetes. Here we describe a study designed to test the efficacy of the Whole Person Model of disease self-management in type 2 diabetes.

**Methods/Design:**

In a parallel-group randomised trial, 180 people with type 2 diabetes of between 2–10 years duration will be recruited via invitation through the Australian National Diabetes Services Scheme. Participants will undergo baseline assessment, followed by randomisation to either intervention or control condition. Control participants will receive fact sheets containing key information about diabetes self-management. The intervention group will receive the INSPIRED (Individual Support & Resources for Diabetes) Manual and be assigned a Health Coach. The INSPIRED Manual consists of six modules that provide key information about diabetes and disease management using the Whole Person Model. Engagement is facilitated by interactive tasks and contact with a Health Coach over seven weeks – an introductory face-to-face session, and six subsequent contacts by phone following each module. Follow-up assessments occur at 13 weeks (post-intervention) and 26 weeks. Primary outcomes include blood glucose management (HbA_1c_), weight and mood. Secondary outcomes include level of exercise, confidence to manage diabetes, and psychosocial well-being.

**Discussion:**

The Whole Person Model is designed to enable health professionals to address mood disturbance without pathologizing any disorders and, in the context of the chronic illness, empowering behavior change and self-management. If proven effective, this model will strengthen capacity of the healthcare workforce to foster and support effective diabetes self-management.

**Trial registration:**

Australia and New Zealand Clinical Trials Register, ACTRN12613000391774

## Background

### Diabetes is a chronic disease

Diabetes mellitus is a metabolic disease with serious implications for both the individual and society. There are currently about 220 million people with diabetes worldwide [1], and the number is projected to exceed 366 million by the year 2030 [2]. Type 2 diabetes accounts for 90–95 percent of cases of diabetes. Although, the specific aetiologies of type 2 diabetes are not known, insulin resistance – that is, where insulin is ineffective in the peripheral tissues – seems to be the major factor, in contrast to absolute insulin deficiency seen in type 1 diabetes [3]. Apart from genetic disposition, the main factors associated with risk of type 2 diabetes appear to be diet, inactivity and body weight – essentially lifestyle factors. Obesity, itself, is associated with insulin resistance. And while the prevalence of obesity is increasing in our communities, there are indications also that type 2 diabetes is increasingly developing earlier in life [4,5]. Type 2 diabetes develops insidiously and often goes undiagnosed for many years because of lack of symptoms in the early stages. It is estimated that up to 6.3 million Americans have undiagnosed diabetes [6].

Diabetes, if undetected or poorly controlled, can result in serious long-term health problems. These include diabetic neuropathy, retinopathy, peripheral vascular disease, renal failure, heart disease and stroke [1]. Worldwide, 2.9 million deaths per year are directly attributable to diabetes, equivalent to 5.2% of world all-cause mortality [7]. Excess mortality attributable to diabetes was over 8% in the U.S.A, Canada and Middle East [7]. Type 2 diabetes is projected to be the leading specific cause of disease burden in Australia for males and second for females by the year 2023 [8].

### Depression and diabetes

Depression is common in people with type 2 diabetes with reported prevalence rates between 9% and 27% [9-11]. This level is about twice as high as that found in the non-diabetic population [12]. The evidence suggests that depression is an independent risk factor for diabetes, with depressed adults having a 37% increased risk of developing type 2 diabetes, compared with those who are not depressed [13]. Clearly there are behavioral factors to partly explain this - for example, depressed people are more likely to be overweight [14], and to exercise less [15]. In addition there are biological factors at play. Potential pathophysiological mechanisms include effects of stress and depression acting via cortisol to stimulate glucose production, increase lipolysis and circulating free fatty acids, decrease insulin secretion, and decrease sensitivity to insulin [16]. Furthermore, depression is associated with increased activity of the pro-inflammatory pathway, and inflammation, also, is associated with insulin resistance [17].

These same mechanisms operate in established diabetes. And in addition to the above, depression interferes with disease management. Depression, and its accompanying feelings of negativity, pessimism, and hopelessness, impairs attention to treatment, diet, exercise etc. [18]. It is very easy for helplessness to set in. Even low levels of depressive symptoms have been shown to be associated with non-adherence to diabetes self-care [19]. Depressive symptoms markedly impair quality of life in both generic and diabetes-specific domains [20] and is associated with higher blood glucose levels [21,22], greater insulin resistance [23], and impaired metabolic control [24]. This, in turn results in more diabetes-related medical complications and higher mortality [25]. Finally, we can note that the presence of depression is associated with an increased cost of diabetes care by 50% [26].

### Chronic disease self-management and the Whole Person Model

The treatment of type 2 diabetes includes weight management, physical activity and dietary modification, together with glucose-lowering medication. To minimize the risk of complications, and to maximize health, regular medical follow-up is required to monitor disease status. This involves regular physical examination (including of feet and eyes), and monitoring of HbA_1c_ and other metabolic risk factors [3]. People with diabetes require a range of services, including primary care physicians, endocrinologists, diabetes educators, dieticians, optometrists and podiatrists; and depending on need, this might include psychiatrists, psychologists, physiotherapists, ophthalmologists, nephrologists, cardiologists and social workers. This can become a full-time occupation for those affected by complicated diabetes and, increasingly, it is recognized that a person with diabetes not only has to manage their illness and comorbidities, emotional distress and lifestyle factors, but also to navigate a complicated health care system, which is not always patient-focused.

Chronic diabetes self-management interventions, including education programs and individual coaching support have been shown to have moderate effectiveness, and vary in their level of intensity [27,28]. Specifically those interventions which incorporate behavioural strategies, and/or ongoing coaching support with a health professional have demonstrated sustained improved outcomes [27,28].

The Diabetes Attitudes Wishes and Needs (DAWN) study [29], a large and ongoing international prospective study of people with diabetes, found the following actions to be important in improving health and quality-of-life for people with diabetes:

•Enhance communications between people with diabetes and healthcare providers

•Promote team-based diabetes care

•Promote active self-management

•Overcome emotional barriers to effective therapy

•Enable better psychological care for people with diabetes.

The Whole Person Model was developed by [name] and [name] [30,31], within a framework of disease self-management, as a mechanism to integrate all these actions. It essentially uses a cognitive behavioural frame, although, in traditional cognitive behavioural therapy (CBT), less emphasis is usually given to the physical components. In the Whole Person Model, it is understood that how individuals feel (sad, anxious, angry or determined) will affect how they think and behave, including with respect to health related behaviours. These in turn affect health, through inadequate adherence to treatment plans and a healthy lifestyle.

The Whole Person Model approach to self-management aims to provide a health promotion self-management program to enable consumers and health professionals to work together and engage in all aspects of their diabetes management. In addition to providing information about the condition and management strategies, it focuses on enabling health promotion strategies to provide the “*how”* to putting these into place. The program anticipates potential barriers, supports strategies to address these barriers and looks at the emotional impact of the condition. It is designed to provide a useful vehicle for addressing diabetes management from the consumer’s perspective. Although not attempting to specifically diagnose or treat depression or anxiety disorders, it does explore emotional responses in the context of diabetes and its management – 'diabetes-specific distress’ [32]. In this way, the worries, frustrations and helplessness that so often arise with diabetes management are targeted, and support is provided to promote active participation and optimal self-management. In this context, we aim to apply the Whole Person Model in a health promotion, self-management program to improve health related behaviours, health outcomes and mood for those with diabetes, and here, in this manuscript, we describe the study protocol for the INSPIRED (Individual Support & Resources for Diabetes) project.

## Methods/Design

### Study aims and hypotheses

The study aims to evaluate, through a parallel-group randomised controlled trial, the efficacy of a type 2 diabetes self-management program, including a resource consisting of the INSPIRED Manual facilitated by seven weekly sessions with a Health Coach. The supported education intervention promotes wellness by facilitating self-management and is designed to enable those individuals with depression to gain understanding and acknowledgement of their emotional struggles. The Health Coaches are qualified Diabetes Educators, trained in the Whole Person Model. It is hypothesized that, compared to those in the control group, the intervention group will demonstrate improvement in the three primary outcomes of blood glucose management (HbA_1c_), weight and mood. We also hypothesize that improvements will occur in exercise level, ability to manage diabetes and psychosocial well-being.

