### Outcomes assessments

Measures will be assessed at baseline, 13 weeks and 26 weeks.

Primary outcome measures will be blood glucose management (HbA_1c_), weight and mood. Secondary outcome measures include level of exercise, confidence to manage diabetes (self-report) and psychosocial well-being (self-report) using validated tools. The research assistant collecting the data will be uninformed of group allocation.

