### Measures

Details about participants, including age, sex, height, education level, employment status and current medications will be obtained at baseline. Weight, waist girth and HbA_1c_, will be measured at each time point (baseline and 13 and 26 weeks). Participants will undergo a blood test at each time point, at Monash Medical Centre, Melbourne, Australia. Normal HbA_1c_ will be assayed on site at Southern Cross Pathology, Monash Medical Centre, Melbourne, Victoria, Australia. Assay instrument is Adams A1C HA-8160 automatic Glycohaemoglobin analyzer. The method is based upon the principles of high performance liquid chromatography (HPLC).

The following validated self-report measures will also be measured at each time point:

•**
*Mood:*
** The Depression, Anxiety and Stress Scale (DASS) [35] is a 21-item scale that assesses three negative emotional states: Depression, Anxiety and Stress and is shown to have excellent psychometric properties in adults [36].

•**
*Experience of demoralisation:*
** The Demoralisation Scale [37] is a 24-item self-report scale with a Cronbach’s alpha of 0.96, measuring depression commonly seen in the physically ill – particularly aspects of helplessness, hopelessness and loss of meaning [37,38].

•**
*Social support:*
** The Multidimensional Scale of Perceived Social Support Scale [39] is a 12-item scale that measures perceived social support from family, friends and significant others. This scale has proven to be psychometrically sound in diverse samples with strong test-retest reliability over a 2–3 month interval (*r* = 0.72 to 0.85), and internal consistencies of the total scale and sub-scales which are high (Cronbach’s Alpha = 0.79 to 0.98) [39].

•**
*Self-efficacy:*
** Diabetes Empowerment Scale – Short Form [40] is an 8-item self-report scale which is a valid and reliable measure of perceived ability to manage the psychological and social demands and challenges associated with diabetes [40]. Higher mean scores indicate greater level of confidence managing one’s diabetes.

•**
*Level of exercise:*
** Participants will be asked to record the total number of steps taken over any three days within a seven day period. This will be measured using a Be Active pedometer (Multifunction Pedometer, WWA2026, Reed Switch Technology) provided to them at the initial assessment. A three day period was noted by Tudor-Locke et al. [41] as a sufficient number of days to reliably measure physical activity in adults.

•**

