### Sample size justification

Using information from comparative studies, 150 participants are required to detect a between group difference of 0.7% (SD ± 1.5) in HbA_1c_, with 80% power and at an alpha level of 0.05 [48]. Similarly, 150 participants are needed to detect a between group difference in weight of 4.4 kg (SD ± 9.6) with 80% power and at an alpha level of 0.05 [49]. Based on a comparative sample using the DASS [50], at least 116 participants are required to detect a hypothesised reduction of 25% in DASS score (20 to 15, SD ± 9.6). On the basis of this analysis, and assuming a dropout rate of 20% based on prior experience, we estimate that a recruited sample of 180 will be required and be sufficient to give the requisite power.

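### Three unranked primary outcomes are sized without any alpha sharing (full 0.05 each) and no success rule is stated, so neither the error rate nor the power of an overall efficacy claim is defined

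*Protocol article*

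**What the plan says.** Under Study aims and hypotheses, the protocol article predicts that, relative to control, "the intervention group will demonstrate improvement in the three primary outcomes of blood glucose management", weight and mood. Outcomes assessments repeats the list without any order: "Primary outcome measures will be blood glucose management (HbA_1c_), weight and mood". The same section adds: "Measures will be assessed at baseline, 13 weeks and 26 weeks". Neither follow-up is called primary. Under Measures, mood is the DASS, which "assesses three negative emotional states: Depression, Anxiety and Stress".

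Sample size justification treats each outcome separately. For HbA1c, "150 participants are required to detect a between group difference of 0.7% (SD ± 1.5) in HbA_1c", and this is done "with 80% power and at an alpha level of 0.05". Weight (4.4 kg, SD 9.6) also gets 150 at the same alpha and power. For mood, "at least 116 participants are required to detect a hypothesised reduction of 25% in DASS score" (20 to 15, SD 9.6), with alpha and power not restated. The recruitment target is 180 with an assumed 20% dropout.

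Statistical analyses plans univariable and multivariable linear regression with covariate adjustment. It gives no hierarchy, multiplicity adjustment or success rule.

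**The concern.** The aim is one overall judgement, the efficacy of the program, and three co-equal outcomes feed into it. Each was sized as if it were the only primary outcome. How the three results combine decides the operating characteristics of the trial:

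- If a win on any outcome counts, 0.05 is the error rate of each test but not of the efficacy claim.
- If all three must win, the error rate is controlled, but 80% power per outcome is not 80% power for the claim.

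A mixed result, such as a benefit on mood but not on HbA1c or weight, therefore has no agreed reading. If the rule is chosen once results are known, a single positive outcome cannot be taken as confirmatory.

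**Working it through.** **Inputs from the article.** Differences and SDs: HbA1c 0.7 and 1.5; weight 4.4 and 9.6; DASS 5 (20 to 15) and 9.6. Allocation 1:1. Recruited 180, dropout 20%, so 180 × 0.8 = 144 completers (72 per arm). Correlations between outcomes, between follow-ups and between baseline and follow-up are not given; those below are assumptions shown as ranges.

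**1. Reproduce the stated sample sizes.** Total N = 4(z₀.₉₇₅ + z₀.₈₀)²(SD/δ)², with (1.960 + 0.842)² = 7.849.
- HbA1c: 4 × 7.849 × (1.5/0.7)² = 144.2, so 73 per arm, 146 (stated 150).
- Weight: 4 × 7.849 × (9.6/4.4)² = 149.5, so 150 (stated 150).
- DASS: 4 × 7.849 × (9.6/5)² = 115.7, so 116 (stated 116).

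All three fit two-sided 0.05 and 80% power. One-sided versions give 114, 118 and 92 and do not fit. The alpha for the DASS is therefore inferred, but with little doubt. No alpha has been shared among the outcomes.

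**2. Any one outcome counts, one time point.** With independent outcomes, 1 − 0.95³ = 14.3%. Simulated with equal correlation between outcomes (1,000,000 draws): about 13.6% at 0.3, 12.5% at 0.5 and 10.9% at 0.7.

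**3. Any one outcome counts, both follow-ups confirmatory.** With six independent tests, 1 − 0.95⁶ = 26.5%. With a correlation over time of 0.5–0.8 and between outcomes of 0–0.5, simulation gives 24.8% down to 19.0%.

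**4. All three must succeed, unadjusted comparison.** At 144 completers the standardised effect is (δ/SD)√(144/4) = 6δ/SD: 2.80, 2.75 and 3.125. Power is Φ(6δ/SD − 1.96): 0.800, 0.785 and 0.878.
- Independent outcomes: 0.800 × 0.785 × 0.878 = 0.551.
- Outcome correlation 0.3, 0.5 and 0.7 (simulated): 0.60, 0.64 and 0.68.
- At 150 evaluable instead of 144: 0.58 with independent outcomes, 0.63 at correlation 0.3 and 0.70 at 0.7.

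**5. All three must succeed, baseline-adjusted.** Adjustment multiplies the SD by √(1 − ρ²), where ρ is the correlation between baseline and follow-up. This treats the stated SDs as SDs of follow-up values. At ρ = 0.6 the factor is 0.8 and the standardised effects become 3.50, 3.44 and 3.91. Power is then 0.938, 0.930 and 0.974, with product 0.85 for independent outcomes. The same steps give 0.76 at ρ = 0.5 and 0.94 at ρ = 0.7.

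**6. Equal split, alpha 0.05/3 = 0.0167, 144 completers.** Per-outcome power from the t distribution for HbA1c, weight and DASS:
- unadjusted: 65%, 63% and 76%;
- baseline-adjusted at ρ = 0.6: 86%, 84% and 93%.

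Unadjusted, 80% power at this level needs 194, 200 and 156 evaluable participants. The chance of at least one win when all three assumed effects are real is nevertheless 97% with independent outcomes and 86% at correlation 0.7, unadjusted.

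**The case against.** The article gives alpha and power outcome by outcome. It states no family-wise error and no joint power, so a reader who infers that one of its figures must be false under any reading goes too far: each test keeps its 0.05 and each outcome keeps its own power. Three separate claims, each confined to its own outcome, would contradict nothing. This stands.

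It is also tempting to say that the trial has either a false-positive rate above 14% or power of only 55–60%. The documents do not support that either. At one time point 14.3% is the value for independence, and positive correlation lowers it. The 55–60% applies only to an unadjusted comparison with weakly correlated outcomes. The planned multivariable regression could include the baseline value, although the article does not name it as a covariate. The two rules are not exhaustive: an alpha split or a hierarchy would also control error.

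A reader might further count ten tests by taking each DASS sub-score at each visit. The sample size section powers a single DASS score, so the document does not make the sub-scores separate primary outcomes. Which score and which visit are primary is mostly detail that an analysis plan not shown here may settle.

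What the objection does not remove is that this document itself fixes three co-equal primary outcomes and a sample size with no alpha sharing. A later plan can add a rule, but the power statement would then have to be redone for that rule.

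**Conclusion.** The point holds as a weakness in how the primary comparison is fixed, not as an arithmetic error: the stated sample sizes reproduce. An efficacy claim resting on any one of the three outcomes carries about 11–14% family-wise error at one time point (outcome correlation 0.7 to 0), and about 19–26% if 13 and 26 weeks both count. A claim requiring all three needs no adjustment of alpha. Its power at 144 completers is about 55–68% unadjusted (outcome correlation 0 to 0.7), or about 76–94% with baseline adjustment and independent outcomes (ρ 0.5–0.7). All ranges rest on assumed correlations. Over the ranges shown, the any-one rule never returns to 5%, whereas the all-three rule can reach 80% if baseline adjustment performs well.

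**What to change.** Choose one rule and write it down before any outcome data are seen by group:

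- **Option A.** Define one confirmatory family: HbA1c, weight and one named DASS score, all at one named time point, with the other time point secondary. Test it with Holm at overall two-sided 0.05.
- **Option B.** State explicitly that all three must succeed, each at two-sided 0.05.

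Under either option, name the baseline value of each outcome as a covariate if it is to be used, and restate power for the chosen rule under that same model, with the assumed baseline correlation given. Do not mix an unadjusted figure for one rule with an adjusted figure for another.

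The cost is wording in the protocol or analysis plan. Under Holm the smallest p-value faces a stricter threshold (0.0167). Under either option the stated power is less favourable unless baseline values are adjusted for. No extra participants are needed.

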### Participant recruitment

Participants with type 2 diabetes will be recruited, via invitation, through the National Diabetes Services Scheme which is a large support scheme for people with diabetes. Approximately 1,098,780 Australians with diabetes are registered with the National Diabetes Services Scheme, of which 86% have been diagnosed with type 2 diabetes. Approximately 6% include those who reside in Victoria, meet inclusion criteria and have nominated to receive information about research opportunities related to diabetes. These individuals will be invited to participate in the project. This method of recruitment will be supplemented by advertisement online via the Diabetes Australia, Victoria website. People will indicate their interest by contacting the research team by telephone. Inclusion criteria are: 1) having had diagnosed type 2 diabetes for between 2 and 10 years, 2) aged 18 years or over, 3) a Body Mass Index (BMI) between 20 and 40, 4) not currently on insulin, 5) sufficient speech and reading fluency in English to read and understand the INSPIRED Manual (determined using the Single Item Literacy Screener [33]), and 6) able to give informed consent. People will be excluded if they have significant cognitive impairment or other infirmity which would obviously preclude their participation. If eligible and willing to participate, potential participants will be met by a research assistant, when consent forms will be signed and baseline measures taken.

